### Randomization

Patients can discontinue the project at any time because of participant request or improving/worsening disease. However, all efforts will be made to avoid missing data. Before starting statistical analyses, the specific way to deal with missing data will be determined at a data review meeting.

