Online rehabilitation reduces the treatment cost and provides 24/7 online support for home exercises [30]. Supporting exercise at home is important because self-management consistency in exercise is a common problem in exercise therapy [31, 32]. Research shows the importance of continuity of exercise at home, because it has positive effects on pain and physical function [32] and cost reduction [30].

To our knowledge, no randomized control trial (RCT) has examined the differences in the effect of PNE with online and face-to-face exercise interventions in people with chronic neck pain. Therefore, the present study aims to investigate the differences between the effect of PNE with online and face-to-face exercise interventions on neck pain and disability, psychological factors, and function in non-traumatic chronic neck pain during COVID-19. We hypothesized that PNE with online exercise intervention could be more effective than PNE with face-to-face exercise intervention on neck pain and disability, psychological factors, and function in non-traumatic chronic neck pain during COVID-19.

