### Outcome variables

All variables will be assessed initially (before intervention), after PNE (after 2 weeks), and after exercise intervention (after 3 months). The flow chart can be seen in Fig. 1. After filling in the questionnaires by the patients, they will be asked about taking any painkillers and psychological medication. The completed questionnaires will be handed over to a skilled psychiatrist who will be blind to assigning patients to study groups. The psychiatrist will consider if it is necessary for any of the patients to take any psychological medication.

Personal information about potential and enrolled participants will be collected, shared, and maintained to protect confidentiality before, during, and after the trial.

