### Primary outcome measurements

The primary outcome will be measured as between- and within-group differences in the Numerical Pain Rating Scale (NPRS) at the second and third assessments.

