#### Numerical Pain Rating Scale (NPRS)

The scale is 11 points for pain reporting. This is the most common pain reporting scale. The patient will choose a number according to the rule (0–10) that best indicates the severity of his pain. The number zero indicates no pain and 10 indicates the most severe or worst pain. (There are different types of numbers from 0 to 10 that one can choose). The scales are categorized as follows: painless (0), mild pain (1–3), moderate pain (4–6), and severe pain (7–10), but these categories do not necessarily reflect the patient’s meanings and for any assessments are poor. These categories may be used to set goals for the outcome of the intervention. NPRS can be done orally (by phone) or graphically. The validity of the NPRS has been shown in patients with rheumatism and other chronic pain conditions (pain > 6 months), ICC has been reported to be 0.95–0.86.40. The MDC reported from the 11-point NPRS is 0.45 [39].

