### Statistical analysis

The study was designed to identify a 2-point difference in pain intensity (30%) assessed by the NPRS across groups, with an expected standard deviation of 2.5 points [55]. For the global perceived effect, there is a difference of 2 points on the scale, with 11 points ranging from − 5 to + 5 [39]. The other specifications were an alpha of 5% and a power of 80%, with a total of 288 patients. However, assuming a 20% drop in follow-up, we will enroll 360 individuals (88 patients per group). G*Power was used to calculate the sample size (GPower 3.0.10, University of Kiel, Germany). The intention-to-treat protocol was followed for post-treatment analysis. See the CONSORT diagram for details.

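### The stopping sentence lets patients leave the whole project because their disease improves or worsens, and nothing shown keeps them in assessment, so outcome-related loss of the NPRS is permitted

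*Protocol article*

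**What the plan says.** The Randomization section of the protocol article has three relevant sentences. The first sets the stopping rule: "Patients can discontinue the project at any time because of participant request or improving/worsening disease". The second states an aim: "However, all efforts will be made to avoid missing data". The third defers the method: "Before starting statistical analyses, the specific way to deal with missing data will be determined at a data review meeting".

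Under Primary outcome measurements, the primary outcome is "between- and within-group differences in the Numerical Pain Rating Scale (NPRS) at the second and third assessments". Outcome variables places those assessments "after PNE (after 2 weeks), and after exercise intervention (after 3 months". Statistical analysis says the post-treatment analysis is by intention to treat, allows for 20% loss to follow-up, and gives the target: "The study was designed to identify a 2-point difference in pain intensity (30%) assessed by the NPRS across groups", with an SD of 2.5.

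The section on the NPRS notes that "NPRS can be done orally (by phone) or graphically". Trial status says that the trial is underway and that completion was planned for 1 May 2022. The article was published on 20 December 2022.

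**The concern.** Stopping treatment and stopping assessment are different events, and the sentence does not separate them. A patient who feels well and stops exercising, or feels worse and stops, may under this wording leave the project altogether. The 2-week or 3-month NPRS is then missing because of what it would have shown.

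Intention to treat needs those scores but does not collect them. The data review meeting can choose how to treat missing scores, but it cannot recover scores that were never taken. Any method it chooses would have to rest on assumptions about patients who left because of their pain.

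Both parts of the primary outcome are exposed. Within an arm, the mean change among completers shifts if more improvers than worseners leave, or the reverse. Between arms, bias can arise if arms differ in who leaves. It can also arise if a real difference exists and patients leave at both extremes of a common scale. The plan expects a real difference: "We hypothesized that PNE with online exercise intervention could be more effective than PNE with face-to-face exercise intervention".

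Three matters are not faulted here: the patient's right to leave, the exclusions for severe pain or missed sessions, and the deferral of the missing-data method.

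**Working it through.** **What the text provides for patients who stop.** Table 1 lists the assessments but has no entry for patients who have stopped. Outcome variables gives assessment times for all variables. Adherence describes motivation, and Post-trial care covers adverse reports and return after the trial. The sentence on avoiding missing data names no procedure. None of these says that a patient who discontinues is still scored.

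**Inputs from Statistical analysis.** SD 2.5, target difference 2 points, 20% loss, 288 evaluable patients. The plan's loss step reproduces: 288 / 0.8 = 360. The plan gives no figure for bias from leaving.

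**Assumptions, not in the documents.** Scores are normal. The correlation rho between tendency to leave and the 3-month score is 0.5, range 0.3 to 0.7. All of the 20% loss is outcome-driven unless stated. Completers are compared.

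**1. Within one arm.** If shares a (improvers) and b (worseners) leave, the completers' mean shifts by rho × 2.5 × (φ(z_a) − φ(z_b)) / (1 − a − b). At rho = 0.5:
- 10% and 10%: 0.
- 15% and 5%: 1.25 × (0.2332 − 0.1031) / 0.8 = 0.20 (0.12 to 0.28 for rho 0.3 to 0.7).
- 20% and 0%, the one-directional extreme: 1.25 × 0.2800 / 0.8 = 0.44 (0.26 to 0.61).

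**2. Between arms, two-tailed leaving on a common scale, true difference 2 points.** Each arm lies 1 point, or 1 / 2.5 = 0.4 SD, from the midpoint. The leaving index therefore has mean −0.4 rho in the better arm and +0.4 rho in the other. A patient leaves if the index exceeds c in absolute value, with c set for 20% loss per arm. At rho = 0.5:
- c = 1.307. The better arm loses 13.4% as improvers and 6.6% as worseners; the other arm is the mirror image.
- Shift per arm: 1.25 × (φ(1.107) − φ(1.507)) / 0.8 = 1.25 × (0.2161 − 0.1281) / 0.8 = 0.138.
- Observed difference: 2 − 2 × 0.138 = 1.72.

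The result is 1.90 at rho = 0.3 and 1.47 at rho = 0.7. If only 10% of patients leave for outcome reasons, rho = 0.5 gives 1.82. With no true difference the bias is 0. Adjusting for the 2-week score (assumed correlation 0.5 with the 3-month score) moves 1.72 to about 1.79.

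**3. Between arms, one-directional leaving.** Here the dropout odds change by a factor exp(0.5) per NPRS point.
- 20% loss in each arm and the same direction: a true 2.0 stays 2.00.
- 30% loss in one arm and 10% in the other, same direction: 1.53 to 2.47.
- Opposite directions in the two arms at 20% loss: 0.99 or 3.01. The document gives no reason to expect this.

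Even where the between-arm difference is untouched, each arm's own mean moves by about (2.00 − 0.99) / 2 = 0.5 points, which matters for the within-group part of the primary outcome.

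**4. Effect on power.** Power is Φ(d / (2.5 × √(2/n)) − 1.96). With 288 / 3 = 96 per arm, it is about 99.7% for 1.72 and 98% for 1.47. Other parts of the article speak of 120 patients. With 20% loss that leaves 96 in total, or 32 per arm, and power is 79% for 1.72 against 89% for 2.0.

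**The case against.** The strongest case is that this is an ambiguous word in a condensed article. The sentence is a permission to patients. It does not say that assessments end or that data are discarded. The general right to leave, stated under Sequence generation, already covers a patient who feels better or worse. The aim of avoiding missing data follows directly, and intention to treat, the fixed assessment times and the phone option all favour the reading that collection continues. Follow-up after stopping is operational detail that a full protocol may contain.

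Much of this stands. The word project may be loose wording for the exercise programme, and the overlap with the right to leave is real. What remains is that the article states a rule, names disease change as a reason under it, and attaches it to the project. The statements on the other side are general, and none says that these patients are scored.

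A reader might infer that the rule necessarily shrinks the observed difference even when loss is equal in all arms. The documents do not support that. Shrinkage follows from the assumed two-tailed model on a common scale; the one-directional model with equal loss leaves 2.0 unchanged. Nor does the 20% in the sample-size section describe outcome-driven loss: it is total loss from any cause. A reader might also infer that the rule removes patients. It only lets them go.

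**Conclusion.** The point holds as a defect of wording with a possible consequence, not as a demonstrated bias. Read literally, the sentence permits outcome-related loss of the 2-week and 3-month NPRS, and nothing in the text shown prevents it.

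Size and direction cannot be derived from the document. The between-arm bias may be zero if leaving is similar across arms. Under the two-tailed model, a true 2-point difference appears as about 1.9 to 1.5. That shift is modest and towards the null, so in this central case it does not manufacture an effect. Larger or opposite biases need arms that differ in how many leave or in which direction. These ranges rest on normal scores, an assumed correlation of 0.3 to 0.7, and treating all of the 20% loss as outcome-driven. Severity is minor to moderate.

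**What to change.** Reword the sentence in the Randomization section so that improvement or worsening may end the exercise programme but not data collection. Seek the NPRS, NDI, PCS and DASS-21 at 2 weeks and 3 months from every randomised patient who has not withdrawn consent, by phone or online form if the patient no longer attends. Include these scores in the intention-to-treat analysis, and record the date and reason for stopping. When a patient should stop exercising remains a clinical decision.

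The cost is a sentence in the protocol and the consent form, a few extra calls or forms, and some dilution of the on-treatment effect.

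If follow-up has closed, as the planned completion date of 1 May 2022 suggests it may have, lost scores cannot be recovered. Then report the timing and reasons for stopping by arm in one table and state the limitation. A sensitivity analysis with shifted imputed scores is optional and can be left to the data review meeting.

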### Allocation concealment mechanism

After the initial evaluation, patients will be randomly assigned to one of three study groups (PNE as an experimental group) and pain biomechanics education (control group) by selecting numbers from 1 to 120, which will be pre-prepared and packaged in sealed envelopes by an independent person. The randomization sequence will not be disclosed until patients complete their baseline assessments. The statistician and the assessor will be blind to the group allocation. Patients will not be blind to the intervention, but do not know which group will be treatment therapy. The three groups in the study will be monitored by a physiotherapist and a corrective movement instructor.

### Post-trial care

The researchers will control any adverse reports by patients through online consulting. Patients will be told to return to the research after the trial if they feel any neck pain or adverse effects.

### Interventions

All sessions of pain neuroscience training and biomedical education for patients in the experimental groups and control group, repectively, will be performed by one of the study researchers, who will be trained in seven training sessions under the supervision of a certified physiotherapist with 10 years of experience. The principles of pain neuroscience and biomedical education, the materials, goals, agenda, and activities of each session are discussed, gathered, and reviewed by two researchers.

### Interventions for experimental groups

For all patients in the two experimental groups, three sessions in 2 weeks will be held to teach PNE as well as how to perform the exercises over a period of approximately 3 months. In the first session, a power point about PNE will be presented to a group of 6 patients, the second session will be home-based online e-learning of PNE, and the third session will be a 30-min one-by-one conversation focused on the patients’ personal needs [27].

The goals of PNE include reducing the severity of pain fear, increasing patients’ awareness of pain, and conceptualizing pain. To achieve this goal, participants must understand that all pain is produced and modulated by the brain and that their pain symptoms are often related to the sensitivity of the central nervous system rather than (persistent) tissue damage [27].

The patient’s understanding of PNE will be asked in the second session. Then, in the third session, the therapist and patient will discuss these responses by relating the material to the PNE, and at the end of the PNE training, patients could put their pain in the correct perspective and feel less at risk of pain. Moreover, tend to do physical activities and not be afraid of or avoid movements.

### Interventions for the control group

Neck biomechanics is focused on clinical neck injuries and is presented by Glomsud et al. and Sokop et al. (112, 113) [34, 35]. Patients are supposed to acquire biomedical knowledge focused on neck pain. The knowledge will be causes of mechanical neck pain; anatomy; physiology and biomechanics of the bones, muscles, and joints of the spine and intervertebral discs; self-care and ergonomic managements; photos that will show the pressure inside the disc and the forces of the joints during daily activities; and postures. Lifting techniques also stretching, strengthing, and endurance exercises will be explained. The questions in the online session will also be related to the patient’s understanding and opinion about the content of the video. In the second session, the patients will be asked about their understanding of the education. In the third session, the therapist and the patient will discuss these answers by relating the questions to the educational material. Patients can also request ergonomic counseling for specific activities or situations, and lifting techniques will be practiced during this session. Patients will recommend being active daily and performing a few common physiotherapy exercises (Tables 1 and 2).

**Table 1 Tab1:** Schedule of enrollment, intervention, study visits, and assessments for both study groups

Time point	Study period			
	Enrolment	Allocation	NPE, 2 weeks	Exercise intervention, 3 months
Enrollment				
Eligibility screen	*			
Informed consent	*			
Baseline assessment	*			
Allocation		*		
Intervention				
NPE			*	
Exercise intervention				*
Assessments				
NRS		*	*	*
NDI		*	*	*
DASS-21		*	*	*
PCS		*	*	*
Function		*	*	*
Adverse events			*	*

**Table 2 Tab2:** Description of the exercises

Exercise	Description	Groups
A	While performing craniocervial flexion, lift the head from the foam between the neck and the mat and maintain this position for a specified period (ten repetitions, 5–6 repetitions, one set).	1, 2, 3
B	In the supine position, apply gentle pressure to the foam between the neck and the mat (ten repetitions, 5–6 repetitions, one set).	1, 2, 3
C	In the supine position, apply gentle pressure to an elastic band, which is placed in front of the forehead and held with both hands (ten repetitions, 5–6 repetitions, one set).	1, 2
D	In the supine position, apply gentle pressure to an elastic band, which is placed behind the head and held with both hands (ten repetitions, 5–6 repetitions, one set).	1, 2
E	In the supine position, hold an elastic band with both hands with the shoulders in the neutral position and the elbows at an angle of ninety, while simultaneously moving the left and right shoulders outward (ten repetitions of 5–6 s, one set).	1, 2
F	Hold the shoulders abducted while holding an elastic band (ten repetitions of 5–6 s, one set).	
G	While performing craniocervical flexion, lift the head from the foam between the neck and the mat and holds this position for a specified period (10 s, one set).	1, 2, 3
H	In the supine position, place an elastic band on the cervical spine from behind and hold it with both hands, applying gentle pressure to it at different levels of the cervical spine (one repetition of 5–6 s per level, one set).	1, 2
I	While performing craniocervical flexion in the supine position, perform flexion, rotation, and extension of the lower part of the cervical spine (ten repetitions of 10 s, one set).	1, 2, 3
J	In the supine position, hold an elastic band with both hands with the shoulders in the neutral position and the elbows at an angle of ninety, while simultaneously moving the left and right shoulders outward (ten repetitions, 10 s, one set).	1, 2
K	In the supine position, flex shoulders with an elastic band resistance (ten repetitions per shoulder).	1, 2
L	Perform craniocervicral flexion in the four kneeling positions while holding the lumbar, thoracic, and cervical spine in a neutral position (ten repetitions of 10 s, one set).	1, 2, 3
M	On four kneeling while performing craniocervical flexion, extend the neck and thorax, retract the shoulders, and flex the elbows (ten 10-s repetitions, one set).	
N	While performing craniocervical flexion, lift the head from the foam between the neck and the mat and maintain this position for a specified period (ten repetitions of 10 s, two sets).	1, 2, 3
O	In the supine position, place an elastic band on the cervical spine from behind and hold it with both hands, applying gentle pressure to it at different levels of the cervical spine (10 s in each level, one set).	1, 2
P	External movements of rotation and diagonal of the shoulders with an elastic band (ten repetitions, two sets).	1, 2
Q	In the four kneeling positions, in the correct alignment of the lumbar spine, neck, and thorax, perform craniocervical flexion (two sets of ten in Yes mode and two sets of ten in No mode).	1, 2
R	In the supine position on a large pilates ball, while performing craniocerebral flexion, extend the thorax and retract the shoulders (ten 10-s repetitions, two sets).	1, 2
S	In the supine position, raise the head for a certain period of time while holding the craniocervical flexion (ten repetitions of 10 s, two sets).	1, 2, 3
T	In the supine position, the person performs rotation and diagonal movements with an elastic band (ten repetitions, two sets).	
U	In the four kneeling positions, while performing the correct alignment of the cervical, thoracic, and lumbar spines, the person performs craniocerebral flexion (ten repetitions, two sets).	
V	In the prone position on a pilates ball, the cranioservital flexion is performed by extending the head with an elastic band resistance (five repetitions per level, holding for 5 to 6 s).	

### Exercise intervention for experimental groups

These exercises will be performed to increase the endurance and strength of the flexor and deep extensor muscles of the neck [36] and the stabilizing muscles of the scapula [37]. These exercises will be presented to the patients during three face-to-face sessions (the first session will discuss only PNE in the experimental groups and neck biomechanics training in the control group). Each exercise is performed from one to four sets of ten repetitions. The number of exercises for each muscle group is added from one exercise in the fourth session to four in the last session. Exercise time will increase from 15 min in the first session to 30 min in the last session. Online group patients are supported and accounted for 24/7 online by the researchers. Also, offline group patients will be answered in person only once a week, and more if necessary. Each group will continue their training interventions for 12 weeks (Tale 2, 3). Borg rating of perceived exertion of 11–13 was chosen to progress the intensity of the training from light to somewhat hard over the 12-week exercise program [38].

All patients will be going to limit their weekly exercise to the study program. The prescheduled exercises will be flexible according to each individual’s progression and limitations (Appendix).

### Outcome variables

All variables will be assessed initially (before intervention), after PNE (after 2 weeks), and after exercise intervention (after 3 months). The flow chart can be seen in Fig. 1. After filling in the questionnaires by the patients, they will be asked about taking any painkillers and psychological medication. The completed questionnaires will be handed over to a skilled psychiatrist who will be blind to assigning patients to study groups. The psychiatrist will consider if it is necessary for any of the patients to take any psychological medication.

Personal information about potential and enrolled participants will be collected, shared, and maintained to protect confidentiality before, during, and after the trial.

### Initial socio-demographic and clinical characteristics of patients

Sex (both males and females)Age (between 18 and 65)Neck pain intensity in accordance with VASNeck pain history (month)Level of studies (no studies, basic education, secondary school, university studies)Employment situation (student, active, active in temporary disability, unemployed, domestic occupation)Marital status (single, widowed, couple, separated or divorced)Weight (kg), height, and body mass index (weight [kg]/height [m^2^])Smoking status (at present, never, before)

